### Data management

All clinical and laboratory data will be recorded in the CRF and stored with a unique serial number identifier. Data will be entered (double data entry) onto
OpenClinica. All data will be regularly backed up and backup copies stored both on and off site. Paper records will be archived in locked cabinets. These cabinets will have limited access with prior authorisation (by the site principal investigator). All data will be partially anonymised prior to presentation or publication of any results. Study participants will be identified by a unique subject identification number but patient identifiable information will not be recorded on the study database in compliance with GCP requirements. The data will be examined for inconsistencies during the trial by the statistician and fed back to study sites for corrections following GCP procedures.

### Confidentiality

All clinical data will be held confidentially, and personal identifiers will be removed before analysis of the data and presentation of the results.

### Data sharing

After completion of the study, requests for data access from researchers outside the study team will be considered by the trial management team and clinical trials unit (Data Governance Committee), and where indicated, requestors will be asked to develop scientific protocols for approval of secondary analyses. The potential to share data will be included in the participant Information and Consent Form (see extended data section)
^
34
^.

### Statistical analysis

The primary analysis for the trial will describe baseline parameters (stratified by study arm) and compare primary and secondary end points by trial arm. The primary analysis will be by intention to treat and secondary analysis will include those treated per protocol (i.e., receiving five days of azithromycin).

The co-primary outcomes are change in CRP (which will be analysed using normal linear regression adjusting for baseline, using appropriate transformations) and microbiological cure (seven day) alone and as a composite with seven-day survival (which will be analysed using logistic regression and exact tests as a binary outcome). Analysis of adverse events and re-admission will use time-to-event methods through day 90 counting in-hospital death as a competing risk. Changes in CRP and other inflammatory markers will be analysed using normal linear regression (potentially on log-transformed data), using generalised estimating equations to jointly model changes at 72 hours and day-seven. Adverse events will also be summarised by body system.

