### Treatment allocation

Following consent, children will be randomly allocated to the treatment arms. Children, on admission to hospital with severe malaria (
*see Inclusion criteria above*) eligible for the trial will be randomised to one of three doses of adjunctive once daily oral azithromycin doses, which will be given for five days in addition to a three-day course of parenteral artesunate.
The comparator cohort with non-severe malaria will receive usual standard of care (oral artemisinin combination therapy). See Study Flow (
Figure 1).

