### Pragmatic dosing chart

Rather than calculate azithromycin doses based on body weight (which in practice is poorly implemented), the trial will use weight bands (see
Table 1) all using 100mg dispersible tablets, which are more practical and generalizable outside of clinical trials.

**Table 1. T1:** Pragmatic dosing chart for dispersible azithromycin.

	10 mg/kg	100mg tabs	15 mg/kg	100mg tabs	20 mg/kg	100mg tabs
Weight (kg)	Weight x10	Tab size	Weight x15	Tab size	Weight x20	Tab size
5.5 - 6.4	55-64	0.5	82.5-97	1	110-129	1
6.5 - 7.4	65-74	0.5	97.5-112	1	130-149	1.5
7.5 - 8.4	75-84	0.5	112.5-127	1	150-169	1.5
8.5 - 9.4	85-94	1	127.5-142	1.5	170-189	1.5
9.5 - 10.4	95-104	1	142.5-157	1.5	190-209	2
10.5 - 11.4	105-114	1	157.5-172	1.5	210-229	2
11.5 - 12.4	115-124	1	172.5-187	1.5	230-249	2.5
12.5 - 13.4	125-134	1	187.5-202	2	250-269	2.5
13.5 - 14.4	135-144	1.5	202.5-217	2	270-289	2.5
14.5 - 15.4	145-154	1.5	217.5-232	2	290-309	3
15.5 -16.4	155-164	1.5	232.5-247	2.5	310-329	3
16.5 - 17.4	165-174	1.5	247.5-262	2.5	330-349	3.5
17.5 - 18.4	175-184	1.5	262.5-277	2.5	350-369	3.5
18.5 - 19.4	185-194	2	277.5-292	3	370-389	3.5
19.5 - 20.4	195-204	2	292.5-307	3	390-409	4
20.5 - 21.4	205-214	2	307.5-322	3	410-429	4
21.5 - 22.4	215-224	2	322.5-337	3	430-449	4.5
22.5 - 23.4	225-234	2	337.5-352	3.5	450-469	4.5
23.5 - 24.4	235-244	2.5	352.5-367	3.5	470-489	4.5
24.5 - 25.4	245-254	2.5	367.5-382	3.5	490-509	5
25.5 - 26.4	255-264	2.5	382.5-397	4	510-529	5
26.5 - 27.4	265-274	2.5	397.5-412	4	530-549	5.5
27.5 - 28.4	275-284	2.5	412.5-427	4	550-569	5.5
28.5 - 29.4	285-294	3	427.5-442	4.5	570-589	5.5
29.5 - 30.4	295-304	3	442.5-457	4.5	590-609	6
30.5 - 31.4	305-314	3	457.5-472	4.5	610-629	6

This weight-band dosing has been developed based on existing data
^
27
^ and will be validated by the nested PKPD sub-study (as has been done in several HIV trials). Children generally tolerate a wide range of azithromycin doses (5-20mg/kg); however, when given in combination with artesunate, doses of 20mg/kg more commonly resulted in vomiting (versus artemether-lumefantrine)
^
28
^. Based on Monte Carlo simulations, we expect that all dose groups should reach the population reference target (adult) AUC24h of at least 3.4 h*mg/L
^
24
^, although there are no data on absorption in severe malaria, which is characterised by impaired gut function
^
25
^, hence the need for this pilot.

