## Trial outcome measures

### Primary outcomes

•  Change in CRP, a putative marker of sepsis at 72 hours (continuous) and microbiological cure (seven-day) (binary), alone and as a composite with seven-day survival.

•  The changes in CRP between day 0 and day 3 as the main endpoint for the PKPD studies.

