### Secondary outcomes

The secondary outcome measures are:

•  Mortality at 48-hours and longer-term survival (to day 28 and to day 90).

•  Length of hospital stay (days)

•  Re-admission to hospital by 90 days

•  Adverse events

•  The population PK of azithromycin and their relation (combined with pathogen susceptibility) with treatment outcome (PD).

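### The per-protocol set requires five days of azithromycin, so it excludes every child who dies before the fifth dose, although the end points include survival

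*Protocol article*

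**What the plan says.** The Statistical analysis section of the protocol article first states that the primary analysis will "compare primary and secondary end points by trial arm". It then says "The primary analysis will be by intention to treat" and adds that "secondary analysis will include those treated per protocol (i.e., receiving five days of azithromycin"). That parenthesis is the whole definition of the per-protocol set.

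Treatment allocation describes "three doses of adjunctive once daily oral azithromycin doses, which will be given for five days".

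Survival enters the end points in two places:
- Primary outcomes list "microbiological cure (seven-day) (binary), alone and as a composite with seven-day survival".
- Secondary outcomes list "Mortality at 48-hours and longer-term survival (to day 28 and to day 90").

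Nothing in the article says how a child who dies during the course is classified per protocol. Nothing limits the per-protocol analysis to outcomes that do not include death.

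**The concern.** Whether a child receives five days of drug is known only after randomisation, and the child must be alive to do so. A set defined that way selects on survival, which is itself part of a co-primary outcome and the whole of the mortality outcomes. The deaths it removes are the early ones. If one dose prevented early deaths and another did not, the per-protocol comparison would discard that evidence.

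The 72-hour CRP end point has a separate timing problem. A child who took every dose due before the sample, but missed a later one, is excluded because of something that happened after the outcome was measured.

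At stake is a secondary analysis that could be read as confirming the primary one. On survival it would show results more favourable than those for all randomised children, and differences between doses smaller than the true ones.

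**Working it through.** The protocol gives no figure for the per-protocol set, so there is nothing to reproduce. The exclusion follows from the definition. Its size can be bounded from figures in the protocol.

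**What follows without numbers.** With once-daily dosing, the fifth dose comes about 4 × 24 = 96 hours after the first.
- A death by 48 hours precedes it, so per-protocol 48-hour mortality is 0 in every arm.
- Only deaths between the fifth dose and day 7 can count against seven-day survival.
- For mortality to day 28 and day 90, every death before the fifth dose is missing.
- The 72-hour CRP sample precedes at least the fifth dose, so membership depends on later dosing.

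**Inputs.**
- 105 children, allocated 1:1:1, with 20% assumed bacteraemic (Sample size determination): 21 with bacteraemia and 84 without.
- Mortality of 6% to 8.5% in the earlier artesunate/quinine trial (Introduction).
- Case fatality of 81/336 = 24.1% with bacterial co-infection and 585/5,760 = 10.2% with malaria alone (Bacterial co-Infection in severe malaria).
- f, the share of deaths that precede the fifth dose. The protocol does not give it, so it is an assumption, shown at 0.5 and 0.9.

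**Expected deaths.** From the two case-fatality rates: 21 × 81/336 = 5.06 and 84 × 585/5,760 = 8.53. The total is 13.59, and 13.59/105 = 12.9%.

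The set loses 105 × m × f deaths, where m is mortality. If all survivors complete the course, per-protocol mortality is m(1 − f)/(1 − mf).

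| m | Deaths in 105 | Removed, f = 0.5 | Removed, f = 0.9 | Intention-to-treat survival | Per-protocol survival, f = 0.5 to 0.9 |
|---|---|---|---|---|---|
| 6% | 6.30 | 3.15 | 5.67 | 94.0% | 96.9% to 99.4% |
| 8.5% | 8.93 | 4.46 | 8.03 | 91.5% | 95.6% to 99.1% |
| 12.9% | 13.59 | 6.80 | 12.23 | 87.1% | 93.1% to 98.5% |

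**Composite in the 21 bacteraemic children.** Assume 80% cure among survivors. By intention to treat, success is (1 − 0.241) × 0.8 = 60.7%. Per protocol it is 0.607/(1 − 0.241f), which is 69.0% at f = 0.5 and 77.5% at f = 0.9.

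**Effect on a dose difference.** Suppose true mortality is 5% in one arm and 20% in another, a 15-point difference (illustration only). Applying m(1 − f)/(1 − mf) to each arm:
- f = 0.5: 11.1% − 2.6% = 8.5 points
- f = 0.75: 5.9% − 1.3% = 4.6 points
- f = 0.9: 2.4% − 0.5% = 1.9 points
- f = 1: 0 points

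**The case against.** Several objections have force.

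- **Intention to treat is primary.** Early deaths count there, so the main result is not biased by this rule. This stands.
- **The scope is inferred.** The sentence about comparing primary and secondary end points describes the primary analysis, and the end points for the per-protocol analysis are not listed. The analysis plan, which is not shown, may narrow them. This also stands. But the article itself fixes the definition, and it exempts neither early deaths nor end points that include survival.
- **No false benefit between arms.** A reader might infer that per-protocol results would favour the drug whatever it does. That is true only of the absolute level of survival. All three arms receive azithromycin. If early death does not depend on dose, removing it from every arm creates no expected difference. The distortion is concealment of a real difference, and it arises from selection on survival, not from misclassified person-time.
- **Vomiting.** A reader might infer from "doses of 20mg/kg more commonly resulted in vomiting" that children would leave the set unequally by arm. The comparator in that sentence is artemether-lumefantrine, not the lower azithromycin doses, and the protocol does not say that children who vomit stop treatment. Unequal drop-out is possible but not stated. The point does not need it.
- **Some values are missing in any set.** A child who dies before the day-three or day-seven sample has no 72-hour CRP or seven-day culture, whichever set is used. This is true, but such a child still has an outcome for mortality and for the composite.
- **Dose choice rests elsewhere.** The PKPD study section bases it on exposure-response modelling in 105 children and does not tie that modelling to the per-protocol set. This limits the consequence.

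**Conclusion.** The point holds for the secondary per-protocol analysis. As written, the set selects on survival to the fifth dose and is unsuitable for any end point that includes death. For 72-hour CRP it selects on dosing after the outcome.

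The zero 48-hour mortality follows from the definition. Seven-day survival is inflated whenever any child dies before the fifth dose. Neither conclusion depends on an assumed rate.

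The size is only a range: about 3 to 12 deaths removed from an expected 6 to 14. It rests on an assumed 50% to 90% of deaths preceding the fifth dose, and on mortality figures from an earlier trial and from a review of other cohorts, which are not restricted to seven days. It would be wrong to take the upper figure of about 13% alone as the expected mortality, because the protocol also cites 6% to 8.5%.

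The documents do not support a claim that the primary analysis is compromised. The definition should be changed, but the matter is moderate.

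**What to change.** Either of two changes to the Statistical analysis section would do.

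1. Define per-protocol adherence separately for each end point: a child is included if all doses due up to the earlier of the end-point time or death were taken. For CRP, count only doses due before the 72-hour sample. Keep children who die early as failures in the cure-plus-survival composite.
2. Keep the five-day-completer set, but limit it to outcomes that do not include death. This is simpler. On its own it leaves the CRP timing problem, so the CRP rule from option 1 should be added.

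Both need one or two sentences and a changed population flag, with no change to treatment. They have costs:
- Under option 1, a child who died after one dose counts as adherent, so the set no longer describes only completed courses.
- Clinical management and monitoring says data on all administered drugs are collected, but children discharged before day five take doses home. Table 2 records drugs received only at 24 hours, 48 hours and discharge, so home doses may not be dated. The rule as written has the same difficulty.
- Trial status says follow-up has ended and the data are being analysed. The trial is open-label, so the change would be post hoc and must be dated and disclosed.

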## Sampling

### Sample size determination

A formal sample size was not calculated. Phase I/II trials are an important step in the assessment of new or existing interventions providing the first data on the feasibility of using a product in a new application. They assess the effect of products (how well they work), and the side effects they may have. They are not usually designed to compare superiority of different products or interventions.

The aim is to generate pilot efficacy data on the optimal azithromycin dose for children with severe malaria, which will inform the design of a later larger Phase III trial. The numbers required to address the trial objectives are therefore balanced against the exposure of children in these settings to a therapeutic intervention (dose) for which there are limited data to date.

The overall sample size for the trial will be 105 children randomised 1:1:1 to receive 10, 15 or 20mg/kg azithromycin (based on weight-bands). This is sufficient for the PKPD sampling and modelling to determine an optimal dose in children with severe malaria using change in CRP at 72 hours, and microbiological cure (seven-day) alone and with seven-day survival. This is under the assumption that 20% of enrolled children (meeting Teule severity criteria) will have bacteraemia and that 80% of these infections will be caused by NTS or other enteric gram-negative organisms based on previous research. 

Based on Monte Carlo simulations, we expect that all dose groups should reach the population reference target (adult) AUC24h of at least 3.4 h*mg/L
^
24
^, although there are no data on absorption in severe malaria, which is characterised by impaired gut function
^
25
^, hence the need for this pilot. Along with the 105 children with Teule criteria we will enrol 50 children meeting other inclusion criteria but without Teule criteria (and without any exclusion criteria) into the control group.

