### Randomisation procedure

Randomisation lists will be generated and kept at the Medical Research Council (MRC) Clinical Trials Unit at University College London, London. The randomisation envelopes will be prepared before the trial, using the lists at the Clinical Trials Facilty, KEMRI Wellcome Trust Research Programme (KWTRP), Kilifi, Kenya. These will be opaque and sealed and will contain a card with allocation. Children will be randomised (1:1:1) to receive 10, 15 or 20 mg/kg azithromycin (based on weight-bands). The cards will be numbered consecutively and opened in numerical order. Clinicians will be aware of the treatment-group dose assignments, but the laboratory tests are to be performed in a blinded manner.

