### Blood sampling schedule

Following consent and randomisation, blood samples will be taken for the following investigations: full blood count, urea and electrolytes, lactate, glucose, malaria status (malaria slide), blood culture and other clinically indicated investigations (not required by the study protocol). Urine will be taken as soon as possible after trial enrolment for multi-stick analysis for assessment of cola or red colour urine and additional storage for later analysis of gut barrier function. In accordance with national guidelines, HIV testing will be performed during admission procedures since this is one of the eligibility criteria. Pre- and post-test counselling will be done in accordance with routine practice. At admission, a venous blood sample will be collected into Heparin and EDTA tubes and stored for subsequent cytokine and biomarker assays, parasitological (
*P. falciparum* HRP2), genetic studies (including sickle cell and glucose-6-phosphatase deficiency status) and immune activation studies (transcriptome and cellular assays). For the latter, red and white cell pellets will be prepared and stored. Further blood samples will be taken at 72 hours, seven days and 28 days (for biomarker assays and immune activation studies); and at day seven for repeat blood culture (see
Table 3). Changes in inflammatory markers (including CRP and procalitonin, PCT) will be measured retrospectively at 72 hours and day seven and microbiology cure measured at day seven (from blood cultures and using non-culture based molecular diagnostics on stored blood).

**Table 3. T3:** Detailed laboratory investigation schedule.

Day from recruitment	D0	D1	D3	D7	D28
Blood culture	3 ml			3 ml (cases)	
PK studies (cases only)	2 x 0.25 ml			1 x 0.25 ml	
Whole blood (Endotoxin)	1.5 ml		1.5 ml	1.5 ml	
Whole blood EDTA (genetics)	1 ml				
Whole blood (transcriptomics, CRP, procalcitonin, calprotectin, gut barrier function)	4.5 ml		2 ml	2 ml	4.5 ml
**Total blood volume research**	**10.4 ml**	**0.5 ml**	**3.5 ml**	**7 ml**	**5 ml**
Urine	x	x	x		

PK, pharmacokinetics; CRP, C-reactive protein.

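### The stated CRP model adjusts for baseline CRP alone; adding the admission blood culture result would recover a little precision at almost no cost.

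*Protocol article*

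**What the plan says.** All places are in the protocol article.

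- **Statistical analysis.** The CRP co-primary is "change in CRP (which will be analysed using normal linear regression adjusting for baseline, using appropriate transformations". Baseline is the only adjustment named. Microbiological cure and its composite with seven-day survival are outcomes "which will be analysed using logistic regression and exact tests as a binary outcome", with no covariate named.
- **Randomisation procedure.** "Children will be randomised (1:1:1) to receive 10, 15 or 20 mg/kg azithromycin (based on weight-bands". No stratification factor is named, and none is ruled out.
- **Blood sampling schedule.** The samples following consent and randomisation cover "full blood count, urea and electrolytes, lactate, glucose, malaria status (malaria slide), blood culture and other clinically indicated investigations". Table 3 schedules a 3 ml blood culture at day 0 and repeats it at day 7 in cases. Admission blood is stored for later HRP2 assay.
- **Sample size determination.** "The overall sample size for the trial will be 105 children randomised 1:1:1", "under the assumption that 20% of enrolled children (meeting Teule severity criteria) will have bacteraemia". The section also says "A formal sample size was not calculated", and of Phase I/II trials that "They are not usually designed to compare superiority of different products or interventions".

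**The concern.** Bacteraemia is the condition the drug is meant to treat, and the protocol treats CRP as a marker of sepsis and as a candidate predictor of co-infection. It therefore expects culture status and CRP to be linked. With 35 children per arm and no named stratification, the expected 21 or so bacteraemic children fall across the arms by chance. Culture could not have been a stratifier, because the article puts time to positivity at two to three days. Adjustment in the model is the available tool, and the stated model does not use it. What is at stake is the precision of the between-arm CRP comparison in a small trial, and how far one unlucky allocation can shift the estimate.

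**Working it through.** There is no figure in the plan to reproduce: no alpha, power, effect size or SD is given. The steps below use the stated counts and mark each assumption.

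**Inputs from the article.** 105 children, 1:1:1, so 105/3 = 35 per arm. Bacteraemia 20%, so 105 × 0.20 = 21, about 7 per arm.

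**Assumptions.** Beyond baseline CRP, culture-positive and culture-negative children differ by d = 0.5 to 1.0 SD in log CRP course (SD within culture groups). All 105 contribute a 72-hour value. Two-sided alpha is 0.05 and power 80%.

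**1. How often the arms are unbalanced.**
- With 21 bacteraemic children spread at random over three arms of 35 (multivariate hypergeometric, 400,000 draws), the largest and smallest arms differ by 5 or more in 39% of allocations and by 7 or more in 12.5%.
- For one given pair of arms (35 each, 20% binomial), a difference of 5 or more has probability 18%.

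**2. What such an imbalance does.** A 5-child difference is 5/35 = 0.143 of an arm. It shifts the contrast by 0.143 × 0.5 = 0.07 SD to 0.143 × 1.0 = 0.14 SD. The standard error of a pairwise difference is √(2/35) = 0.239 SD, so the shift is about 0.3 to 0.6 of a standard error.

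**3. Variance explained by culture.** With prevalence p = 0.20, culture contributes p(1 − p)d² = 0.16d² to a residual variance of 1 + 0.16d².

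| d (assumed) | 0.16d² | R² = 0.16d²/(1 + 0.16d²) | Equivalent n = 105/(1 − R²) |
|---|---|---|---|
| 0.5 | 0.04 | 0.04/1.04 = 3.8% | 109 |
| 1.0 | 0.16 | 0.16/1.16 = 13.8% | 122 |

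**4. Detectable pairwise difference.** In units of the baseline-only residual SD, it is (1.960 + 0.842) × 0.239 = 0.67 without culture. With culture it is 0.67 × √(1 − 0.038) = 0.66 at d = 0.5, and 0.67 × √(1 − 0.138) = 0.62 at d = 1.0.

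**5. Cost.** The baseline-only model has four parameters (intercept, two for arm, one for baseline). Culture adds one, so residual degrees of freedom go from 101 to 100.

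**6. Whether the same remedy suits the binary outcomes.**
- *Cure.* Among 21 bacteraemic children, assumed cure rates of 90% to 70% leave 21 × 0.10 = 2.1 to 21 × 0.30 = 6.3 non-cures.
- *Deaths.* The case-fatality rates in the article's systematic review give 21 × 0.241 + 84 × 0.102 = 13.6. The 6 to 8.5% mortality it cites from the artesunate trial gives 105 × 0.06 = 6.3 to 105 × 0.085 = 8.9. Neither is a seven-day rate for this population.
- These counts do not support additional covariates.

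**The case against.** The strongest reply is that nothing here is an error. Baseline-adjusted linear regression with a suitable transformation is a standard analysis. Omitting a prognostic variable leaves a randomised comparison unbiased with valid type I error, and chance imbalance is already reflected in the standard error. The article is condensed, and a fuller covariate list may sit in the analysis plan. The trial makes no claim to be sized for superiority. All of this stands, and it limits the point to one of efficiency. What survives is that the article does state a covariate choice for a co-primary outcome, and that a better one is available from a sample already scheduled.

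Baseline CRP will also absorb part of any culture effect, and the article itself describes blood culture as insensitive. Both shrink the gain towards the lower end of the range; neither makes the adjustment invalid.

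Several stronger readings are tempting and are not supported:

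- **That the dose choice is compromised.** The PKPD study section rests that choice mainly on exposure–response modelling, not on the arm contrast alone.
- **That imbalance of 5 or more affects 39% of comparisons.** That figure is for the largest against the smallest arm; a given pair is at about 18%.
- **That adjustment could recover 20 to 30% of the variance.** The assumed culture effect yields at most about 14%.
- **That the binary co-primaries need covariates too.** Events are too few, and admission culture largely defines who can be cured, so there it acts more as a population restriction than as a covariate.
- **That parasite burden is already held for every child.** The slide is listed for malaria status with no density stated, and HRP2 depends on later assay of stored blood.
- **That hours to the day-3 sample belong in the model.** That is a post-randomisation variable.

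**Conclusion.** The point holds as a modest loss of efficiency in the CRP co-primary, not as a bias, a type I error problem or a contradiction. On the assumed 0.5 to 1.0 SD culture effect beyond baseline CRP, adjustment is worth about 4 to 17 extra children on 105 and lowers the pairwise detectable difference from 0.67 to between 0.66 and 0.62 SD. It also protects against the shift of 0.07 to 0.14 SD that a 5-child imbalance would cause. The size rests wholly on that assumed effect, on the protocol's 20% bacteraemia rate, and on nearly complete 72-hour CRP. If the effect beyond baseline CRP is smaller, so is the gain. The conclusion concerns what the article states; an analysis plan that already names culture would settle it.

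**What to change.** Specify the CRP co-primary as log CRP at 72 hours regressed on arm, log baseline CRP and admission culture (positive or negative). Optionally add log PfHRP2 if it is assayed in all children. With log baseline in the model, the arm effect is the same whether the outcome is log 72-hour CRP or change in log CRP, so the endpoint is unaltered. Report the baseline-only model as a sensitivity analysis.

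First confirm that the day-0 culture and biomarker samples were drawn before the first azithromycin dose: the article places sampling after randomisation and does not state its order relative to dosing. Leave logistic regression and exact tests for the binary co-primaries as they are.

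The cost is a sentence in the analysis plan and one degree of freedom (two with PfHRP2); the culture needs no new sample. Because the Trial status section says follow-up is complete and the data are being analysed, the addition should be dated, and labelled post hoc if CRP by arm has already been seen.

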## Sub-studies

### PKPD study

For PK analysis, model-based sampling strategies will enable the description of both intra- and inter-patient variability. A maximum of 3x 0.2ml samples will be taken from each subject on two occasions between day one to five around meaningful time points to describe the PK throughout a dosing interval plus one sample at follow up on day seven to determine the elimination of azithromycin after end of treatment (a total of seven samples per patient). In the first year we will develop highly sensitive bioanalytical assays using ultra performance liquid chromatography coupled with tandem mass spectrometry (UPLC-MS) for determination of azithromycin in stored microvolumes of plasma (analysis performed at Radboud University, Nijmegen). 

Initially a population PK model will be developed for azithromycin and will investigate possible covariates for its PK. This will be followed by an investigation of the relationship between plasma PK and PD using the developed PK model, known MIC-values since the area under the curve (AUC):MIC ratio is the pharmacodynamic driver for azithromycin
^
16,
30
^ and the treatment outcomes (changes in CRP at day three and microbiologic cure and/or mortality at day seven). Based on Monte Carlo simulations, we expect that all dose groups should reach the population reference target (adult) AUC24h of at least 3.4 h*mg/L
^
24
^, although there are no data on absorption in severe malaria, which is characterised by impaired gut function
^
25
^, hence the need for this pilot. The different doses in 105 children provides variability in exposure so that we identify whether all doses are in the flat part of the exposure-response curve, in which case the lowest dose will be chosen. Other secondary endpoints include mortality at 48 hours, length of hospital stay (days), re-hospitalisation and other adverse events. Quality-control of stored bacterial isolates, non-culture (molecular) assessment of bacterial infection including the determination of MIC to inform PKPD studies will be batch-processed at KWTRP, Kenya.

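### For seven-day microbiological cure alone, logistic regression may give no finite odds ratio between arms, because only about seven children per arm can inform it (minor)

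*Protocol article*

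**What the plan says.** The Statistical analysis section of the protocol article makes change in CRP and microbiological cure co-primary. The binary part is "microbiological cure (seven day) alone and as a composite with seven-day survival", and both versions fall under the same method statement: "which will be analysed using logistic regression and exact tests as a binary outcome". The section also says that "The primary analysis will be by intention to treat". It does not say which children form the denominator for cure, or whether dose enters the model as three categories or as a trend.

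Under Sample size determination, "The overall sample size for the trial will be 105 children randomised 1:1:1 to receive 10, 15 or 20mg/kg azithromycin". Two premises go with this number. On prevalence, the text supposes "20% of enrolled children (meeting Teule severity criteria) will have bacteraemia". On the organisms expected in those children, it supposes "80% of these infections will be caused by NTS or other enteric gram-negative organisms". The same section states that "A formal sample size was not calculated" and describes the aim as pilot efficacy data for a later Phase III trial.

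The PKPD study section will relate plasma exposure to "treatment outcomes (changes in CRP at day three and microbiologic cure and/or mortality at day seven". It names no regression model for that step.

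**The concern.** A child can fail microbiologically at day seven only if an infection was there to clear. Cure is therefore informed by the bacteraemic children, a small fraction of those randomised. If one arm has no failures among them, the likelihood of a logistic model with arm as a category has no finite maximum. The fitted log odds ratio runs off to a large arbitrary value, and its Wald interval means nothing.

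A dose-finding pilot is useful mainly for its estimates and intervals. If the only named method that yields an effect estimate breaks down, the report on cure may contain a p-value and nothing about the size or precision of the dose effect.

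**Working it through.** **Inputs from the protocol.** 105 children randomised 1:1:1 gives 35 per arm. Bacteraemia is assumed in 20%, so 105 × 0.20 = 21 children, or 35 × 0.20 = 7 per arm. If only the 80% with NTS or other enteric gram-negative infection count, this is 5.6 per arm. The protocol states no cure rate and no power, so there is no figure of its own to reproduce.

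**Assumption.** The non-cure rate f among bacteraemic children is not given. It is scanned below and taken as equal in all arms.

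**Chance of an empty arm, cure alone.** Let the bacteraemic number per arm vary as Binomial(35, 0.20). One arm then has no failures with probability q = (1 − 0.2f)^35. At least one of three arms is empty with probability 1 − (1 − q)³. With exactly 7 per arm, q = (1 − f)^7.

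| f | q, number varies | at least one arm empty | same, exactly 7 per arm |
|---|---|---|---|
| 5% | 0.703 | 97% | 97% |
| 10% | 0.493 | 87% | 86% |
| 20% | 0.240 | 56% | 51% |
| 30% | 0.115 | 31% | 23% |
| 40% | 0.054 | 15% | 8% |

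Counting arms in which every bacteraemic child fails, which are also inestimable, moves 31% to 32% and leaves 87% and 56% unchanged.

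**Threshold.** The probability equals 50% when q = 1 − 0.5^(1/3) = 0.206. This gives f = 20.2% with exactly 7 per arm and f = 22.0% when the number varies.

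**Infinite or undefined.** All three arms are empty with probability q³: 0.493³ = 12% at f = 10%, and 35% at f = 5%. In those trials every odds ratio is undefined. If one arm only is empty, the two contrasts involving it are infinite and the third is still estimable.

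**What the fit does.** An ordinary maximum-likelihood fit to 0/7, 2/7 and 1/7 failures gave log odds ratios of about 21 with standard errors of about 18,000.

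**What the exact test does.** Fisher's test on 7 versus 7 stays valid with an empty cell: 0 versus 2 failures gives p = 0.46, 0 versus 3 gives 0.19, 0 versus 4 gives 0.070 and 0 versus 5 gives 0.021.

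**Larger denominator.** For cure alone, counting all 35 children per arm adds only non-failures. At 10% non-cure the overall failure rate is 0.20 × 0.10 = 2%, and q = 0.98^35 = 0.493, the same as above.

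**Composite with survival, all 35 per arm.** Deaths in non-bacteraemic children now count, with q = (1 − m)^35 for overall failure m.
- m = 6% (lower mortality figure quoted in the Introduction from the earlier artesunate–quinine trial): q = 0.115, 31%.
- m = 8.5% (upper figure): 13%.
- m = 0.20 × 24.1% + 0.80 × 10.2% = 13.0% (case fatalities from the review of bacterial co-infection in the Introduction): 2%.

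These mortality figures are proxies, not seven-day rates.

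**Composite in bacteraemic children only.** Taking 24.1% as the minimum failure rate gives 38% with exactly 7 per arm and 44% when the number varies.

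**The case against.** The strongest reply is that the plan already provides for sparse data by naming exact tests beside logistic regression, and that the fitting method and interval are details for a statistical analysis plan. Much of this stands. Logistic regression is not the only method, inference by p-value is protected, and exact tests can be inverted to give intervals. But the protocol does not leave the estimator open. It names logistic regression, which unqualified normally means maximum likelihood, and it does not mention inverting the tests. An analysis plan that follows the text literally inherits the problem.

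Several stronger readings are tempting and are not supported:

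- *The protocol's own figures imply an empty arm in most trials.* They do not. The bacteraemia figure alone is not enough; a non-cure rate is needed, and the result runs from 97% to 15% as f goes from 5% to 40%. Cure is also to be assessed by molecular methods as well as culture, and the Introduction says that culture misses cases, so the number of infected children could exceed 21. Early deaths work the other way, since children who die have no day-seven sample.
- *The whole binary co-primary fails.* The composite over all randomised children is largely spared.
- *The exposure–cure model fails in the same way.* The PKPD section names no logistic model, and a continuous exposure does not separate merely because one arm is empty. In a simulation with no exposure effect and an assumed log-normal spread (SD 0.5) around dose, separation occurred in about 15% of trials at 10% non-cure and 2% at 20%. Dose fitted as a linear trend across arms gave about 37% and 10%.
- *The Phase III design is undermined.* The Discussion foresees mortality as the Phase III primary outcome, and change in CRP is the main PKPD endpoint here.

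**Conclusion.** The point holds in a narrow form and is minor. For cure alone, compared by arm as a category, the one named method that gives an effect estimate has a substantial chance of giving no finite odds ratio. That chance exceeds one half when non-cure is below about 20 to 22%. The conclusion rests on the protocol's 20% bacteraemia, on an assumed non-cure rate equal across arms, and on maximum-likelihood fitting. It is a weakness in the choice of estimator. It does not invalidate the exact tests and does not extend to the composite over all randomised children or to the exposure–response work.

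**What to change.** For microbiological cure alone, state that the arm effect will be estimated by Firth penalised-likelihood logistic regression with profile-likelihood intervals, or by exact logistic regression. Keep the exact tests. Report exact confidence intervals for the cure proportion in each arm and for the differences between arms.

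Two small examples show what this gives:
- With arm as a category, the Firth estimate amounts to adding one half to each cell. For 2/7 versus 0/7 failures the odds ratio is (2.5/5.5)/(0.5/7.5) = 6.8, where maximum likelihood gives infinity.
- For 7 cures out of 7, the exact 95% interval for the cure proportion runs from 0.025^(1/7) = 59% to 100%.

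The change is one or two sentences, uses standard software and needs no new data. The article reports recruitment and follow-up as complete and analysis as under way, so the change should be dated and described as a choice of estimator prompted by the expected counts. The price is slight shrinkage of the estimate and wide intervals, which properly reflect about seven informative children per arm.
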